## Interventions

### High–definition transcranial direct current stimulation (HD-tDCS) group

Trained nurses will administer the intervention and provide instructions for participants to receive either active or sham HD-tDCS treatment (Soterix medical, Inc., Woodbridge, NJ, USA) under the same instructions during all sessions for 2 weeks. All participants will be treated using the same device model. The HD-tDCS device is capable of being portable and wirelessly controlled through computer software developed by the manufacturer. The montages will be arranged in a “4 × 1 ring set-up,” which is the most commonly utilized HD-tDCS setting. The center anode electrode is surrounded by four return cathode electrodes. The anode will be positioned over the left DLPFC, which is located at F3 according to the 10/20 electroencephalogram system. The four cathodal electrodes will be placed at FC1, AF3, F7, and FC5 (Additional file 1). The designated electrode stimulation areas on the scalp will be coated with conductive electrode gel. The electrodes will be secured in place by using caps that are appropriate for the head size of each participant. Impedance checks will be performed prior to each treatment session. A 2-mA stimulation will be administered for a duration of 20 min, with the current gradually ramping up and down over a period of 30 s. The patients will be instructed to maintain a relaxed and immobile state throughout the intervention. The administrator will closely monitor the impedance levels throughout each session and document any adverse reactions reported by the participants. The participants will be granted a 5-min rest period following the intervention and will be actively queried regarding any discomfort they may experience. Each session will have a duration of approximately 30 min, and there will be a total of 10 sessions (consisting of two consecutive weeks of treatment, with 5 days per week).

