**Methods:**

MDD patients with ADS will be recruited and randomly assigned to the active HD-tDCS or sham HD-tDCS group. In both groups, patients will receive the active or sham intervention in addition to their pre-existing antidepressant therapy, for 2 weeks with 5 sessions per week, each lasting 30 min. The primary outcome measures will be the change of depressive symptoms, clinical response, and the remission rate as measured with the 17-item Hamilton Depression Rating Scale (HDRS-17) before and after the intervention and at the 2nd and 6th week after the completed intervention. Secondary outcome measures include anxiety symptoms, cognitive symptoms, disability assessment, and adverse effects.

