### Randomization, concealment, and blinding

The eligibility participants will be randomly assigned to either active or sham HD-tDCS group with a 1:1 allocation. This study will use the Statistical Analysis Software (version 9.3, SAS Institute Inc., Cary, NC, USA) to generate the random allocation sequence. The randomization list will be enclosed in computer-generated opaque envelopes, each labeled with a sequence number on the outside. After the eligible patients have been screened, the researchers will proceed to open the envelopes. The unblinded researchers will create the randomization sequence and allocate participants to treatments. The trained operators responsible for administering HD-tDCS will not be blinded to allocation and, as a result, will be excluded from assessments and data processing. The participants, statisticians, and evaluators will be kept blinded to the treatment allocation. The unblinding process should only be initiated in the event of an emergency, such as the occurrence of any serious adverse events.

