### Sham–control HD-tDCS group

The procedure for sham stimulation will be identical, with the exception that the electrical current will gradually decrease to zero after 30 s, thereby producing an equivalent initial sensation of HD-tDCS. The stimulator will be programmed to automatically control the current, eliminating the need for operator intervention. The computer will be positioned posterior to the subjects’ craniums, thereby obstructing their visual access to the readout.

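### Unblinded HD-tDCS operators are excluded from assessments in one section but document participants' adverse reactions in another, which leaves the session-level adverse-effect data open to recording bias

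*Protocol article*

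**What the plan says.** Under Randomization, concealment, and blinding, the protocol article states: "The trained operators responsible for administering HD-tDCS will not be blinded to allocation and, as a result, will be excluded from assessments and data processing". It then lists who is blinded, and operators are not on the list: "The participants, statisticians, and evaluators will be kept blinded to the treatment allocation".

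Under the HD-tDCS group heading in Interventions, delivery is given to nurses: "Trained nurses will administer the intervention and provide instructions for participants to receive either active or sham HD-tDCS treatment". The same paragraph gives the person delivering the session a recording task: "The administrator will closely monitor the impedance levels throughout each session and document any adverse reactions reported by the participants". After a short rest the participants "will be actively queried regarding any discomfort they may experience"; the sentence does not say by whom. The Sham-control section makes the sham procedure the same except for the current.

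The abstract makes the resulting data an outcome: "Secondary outcome measures include anxiety symptoms, cognitive symptoms, disability assessment, and adverse effects". Under Adverse effects and risk indicators, a checklist (Additional file 2) is used at every session; the person completing it is not named. Table 1 places the checklist under Assessments, at T1.

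**The concern.** The blinding section gives its own reason for the exclusion: operators know the arm, so they should not assess. The intervention section then has them document the content of a secondary outcome.

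The reactions in question, such as the itching, tingling and headache named in the pilot summary, are subjective. How often they appear in the record depends partly on how they are asked about, how far a vague report is pursued, and what is judged worth writing down. Someone who knows the arm can do each of these differently by arm without intending to. An operator who expects active stimulation to be felt may probe more in that arm and create an excess. An operator who favours the treatment may record less there and hide a real difference.

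At stake is the between-arm tolerability comparison. The pilot made such a comparison, and the Discussion anticipates a favourable result on adverse effects.

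**Working it through.** No sample size, power or alpha figure depends on this point, so there is nothing to recompute. The check sets the statements side by side.

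1. **Who is unblinded?** The operators responsible for administering HD-tDCS (Randomization, concealment, and blinding). Only participants, statisticians and evaluators are kept blinded.
2. **Who is the administrator?** Trained nurses administer the sessions (HD-tDCS group). The operators in step 1 are defined by that same task, so the administrator is the unblinded operator.
3. **What may that person not do?** Such operators "will not be blinded to allocation and, as a result, will be excluded from assessments and data processing".
4. **What is that person told to do?** Document the adverse reactions that participants report, in each session (HD-tDCS group).
5. **Does this apply in both arms?** Yes. The sham procedure is stated to be identical except for the current.
6. **Is it an assessment of an outcome?** Yes. The abstract lists adverse effects as a secondary outcome, the Discussion repeats them among the secondary objectives, and Table 1 lists the checklist under Assessments.
7. **Does any section give session-level recording to a blinded person?** No. The checklist and the post-session query are described without an actor, and the only named recorder is the administrator.
8. **Does automation remove the problem?** The sham section says: "The stimulator will be programmed to automatically control the current, eliminating the need for operator intervention". That concerns control of the current. The blinding section still declares the operators unblinded.
9. **How far does it reach?** The YMRS also falls under adverse effects. It is observer-administered and nothing assigns it to operators, so it is outside this point.

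Steps 1 to 4 conflict as written. Steps 5 to 7 show that the conflict concerns outcome data in both arms, and steps 8 and 9 set its limits.

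**The case against.** The strongest reply is that this is ordinary chairside safety logging. Someone present must note a reaction during stimulation, and the exclusion from assessments could be read as covering only the evaluators' rating scales. The reactions are also reported by participants, who are blinded, so the operator may do little more than transcribe. A condensed article may leave the assignment of the checklist to the full protocol or to Additional file 2.

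Much of this stands. It narrows the risk to eliciting, grading and recording, and an operator must remain free to log and escalate a reaction. It does not remove the conflict: the only named recorder of session reactions is unblinded, the data belong to a named outcome, and a document not shown cannot make two published statements agree.

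Stronger readings are tempting, but the documents do not support them:

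- **The whole adverse-effect outcome is assessed unblinded.** This is not shown. The YMRS is not assigned to operators. That the operator completes the checklist or asks about discomfort after the session is a natural reading, but it is not stated.
- **HDRS-17 is compromised.** Its evaluators are blinded. Any cueing of participants would come from operators being unblinded at all, which the article declares openly, and would be the same whoever writes down the reactions. The article also keeps instructions the same across sessions, hides the readout from participants, and schedules a blinding assessment at T3.
- **The bias can be expressed as a number.** Counting 58 × 10 = 580 affected checklists would assume that the operator completes every one and that nobody drops out, although the sample size section allows for 20% drop-out. Any false difference in rates would need capture probabilities that the documents do not give.
- **Operator unblinding was avoidable.** Automatic control of the current does not show that the device can conceal the arm from the person running it.

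**Conclusion.** The point holds for session-level adverse reactions. The protocol article contradicts itself on whether unblinded operators take part in assessments, and the contradiction falls on part of a secondary outcome, at each of the ten planned sessions per participant and in both arms.

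The direction of any bias is unknown and its size cannot be estimated from the documents. Blinded participants as the source of the reports limit it. The conclusion assumes that the administrator of the intervention section is the operator of the blinding section, which follows from the shared task, and that no blinded session-level record exists elsewhere, since none is described. The sample size and the primary analysis are not touched.

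This is a clear inconsistency with a cheap remedy, and it should be put right before a tolerability comparison is reported.

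**What to change.** - Have the participant, who is blinded, complete the existing checklist (Additional file 2) after each session. State that this record is the source for the between-arm tolerability comparison.
- Limit the operator to monitoring the device and to logging and escalating events for immediate safety. Amend the HD-tDCS group section so that it agrees with the blinding section.
- If operator recording is kept, or for sessions already recorded that way, state that session-level adverse-effect data were collected unblinded and limit the tolerability conclusion accordingly.

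The cost is a few minutes of participant time per session and a short protocol amendment. It uses the checklist already in the plan and leaves the sample size, the intervention and the visit schedule as they are. Self-completion is preferable to giving the checklist to the blinded evaluators: hearing about stimulation sensations after every session could unblind them for HDRS-17, and it would use extra staff time.

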### Sham–control HD-tDCS group

The procedure for sham stimulation will be identical, with the exception that the electrical current will gradually decrease to zero after 30 s, thereby producing an equivalent initial sensation of HD-tDCS. The stimulator will be programmed to automatically control the current, eliminating the need for operator intervention. The computer will be positioned posterior to the subjects’ craniums, thereby obstructing their visual access to the readout.

#### Criteria for discontinuing or modifying allocated interventions

There will be no special criteria for discontinuing or modifying allocated interventions.

#### Relevant concomitant care permitted or prohibited during the trial

Implementing HD-tDCS treatment or sham-controlled antidepressant augmentation will not require alteration to usual care pathways (including use of any medication), and these will continue for both trial arms.

#### Provisions for post-trial care

The patients will receive notification of their allocated arm (treatment or sham) at the conclusion of the study. Furthermore, participants will continue to receive standard care as determined by the treating psychiatrist or care team. It typically entails a combination of behavioral therapies, psychosocial interventions, and psychotropic medications.

## Outcomes

### Diagnostic interview

The diagnoses will be confirmed through a semi-structured psychiatric diagnostic assessment, conducted by an experienced psychiatrist using the validated Chinese-bilingual version of the Structured Clinical Interview for DSM Mental Disorders in accordance with DSM-5.

### Demographic data

The participants’ fundamental demographic information, encompassing age, gender, educational attainment, birthplace, marital status, offspring count, financial standing, family history of affective disorders, and household income will be obtained upon enrollment into the study. Details of the subjects’ psychiatric history, including the age at onset of their initial depressive episode, number of relapse episodes, and current medication and dosage, will be documented during the baseline assessment. The medical history and treatment of patients will be evaluated through direct inquiry and confirmed with their electronic health records in the hospital authority.

### Primary outcome

The primary outcome will be the change of depressive symptoms. The clinical response rate and remission rate, as assessed by the HDRS-17 (17-item Hamilton Depression Rating Scale) at 6 weeks post-intervention were measured. The Chinese version of HDRS-17 has been validated for its psychometric properties and is commonly used to evaluate depressive severity in Chinese patients with depression symptoms [18]. The clinical response is defined as a ≥ 50% reduction from the baseline [19], and a score of 7 or less will be used as an indicator of remission [20].

### Secondary outcomes

#### Anxiety symptoms

Anxiety symptoms will be measured by the DSM-5 Anxious Distress Specifier Interview (DADSI), which is more brief than the HAMA (Hamilton Anxiety Scale) and may prove to be a more practical tool in clinical settings [21]. The DADSI probes evaluate the five symptoms of the anxious distress specifier and inquire about symptom presence and severity over the past week, which also determine whether the symptom is present for a majority of the depressive episode. Item severity for the past week is rated from 0 to 4 (0 = not at all true, 1 = rarely true, 2 = sometimes true, 3 = often true, 4 = almost always true) [22]. The DADSI is a reliable and valid measure for assessing the presence of the DSM-5 anxious distress specifier in individuals with MDD as well as evaluating the severity of its associated features [22]. Both the DADSI and HAMA were valid measures of anxiety severity in depressed patients; however, the HAMA exhibited a higher degree of confounding with depression measures compared to the DADSI [21]. Earlier studies [4, 23] have shown that the ADS exhibits satisfactory internal consistency (Cronbach’s = 0.71) and predictive validity for subsequent course and treatment response in depressed patients [24].

#### Cognition

For the assessment of cognitive status in MDD patients with ADS, a battery of neurocognitive tools such as the Repeatable Battery for the Assessment of Neuropsychological Status (RBANS) [25] is utilized, encompassing various domains including attention, immediate and delayed memory, language, and visuospatial/constructional abilities. The Chinese version of RBANS has been certified as a reliable tool for assessing cognitive function with reasonable reliability and validity. Higher scores indicate better neurocognitive status.

#### Disability assessment/daily functioning

Disability was evaluated using the WHO Disability Assessment Schedule (WHODAS 2.0), a tool that has demonstrated good reliability and validity in assessing adults from diverse cultural backgrounds [26]. In China, disability caused by mental disorders is clearly defined based on the duration of the disorder and the individual’s score on WHODAS. The WHODAS 2.0 full version comprises of 36 questions that evaluate six domains, namely cognition (communication and thinking activities), mobility (standing, moving around inside the home, getting out of the home, and walking a long distance), self-care (hygiene, dressing, eating, and staying alone), getting along with others (interactions with other people), life activities (domestic responsibilities, leisure, work, and school), and participation (joining in community activities and participating in society).

#### Adverse effects and risk indicators

The Young Mania Rating Scale (YMRS) [27] will be utilized to detect treatment-induced manic or hypomanic episodes, an 11-item observer-administered scale of mania intensity. YMRS ranges from 0 to 60, with higher scores indicating greater severity. The minimum score required to define a new-onset mania or hypomania is 8 points. A checklist of potential adverse effects associated with the administration of HD-tDCS will be compiled based on available literature [28, 29]. The checklist (Additional file 2) will be utilized to monitor the tolerability and adverse events in each session throughout the intervention. The assessment of risk indicators, such as suicidal ideation or severe self-neglect, will be conducted directly to determine the need for immediate changes in treatment based on identified risks and needs.

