### Results from our pilot study

A pilot study [14] was conducted by our team in 39 adults who have MDD with ADS received five consecutive daily sessions of 20-min active or sham HD-tDCS interventions weekly for 2 weeks. The results revealed that the HD-tDCS has significant efficacy in the treatment among MDD patients with anxious distress. The rate of adverse events(e.g., itching, tingling and headache) showed no significant differences between the two groups. Additionally, no severe adverse events or mania was reported. Nevertheless, it should be noted that the trial was of short duration, limited to hospitalized patients, and did not include an evaluation of cognitive or daily functioning. A double-blinded randomized controlled trial (RCT) with an adequate sample size and adequate study periods is warranted to confirm the efficacy of HD-tDCS as an augmentation therapy with antidepressants in MDD patients with ADS.

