**Assessments:**					
*Primary outcome*					
HDRS-17	X	X	X	X	X
*Secondary outcomes*					
DADSI		X	X	X	X
RBANS		X	X	X	X
WHODAS 2.0		X	X	X	X
*Adverse effects*					
YMRS	X		X	X	X
Adverse checklist			X		
Pregnancy test	X				
Patients’ compliance			X	X	X
Blinding assessment					X

X represents data collection timepoint

*HDRS-17* 17-item Hamilton Depression Rating Scale, *DADSI* the DSM-5 Anxious Distress Specifier Interview, *RBANS* the Repeatable Battery for the Assessment of Neuropsychological Status, *WHODAS 2.0* the WHO Disability Assessment Schedule 2.0; *YMRS*, the Young Mania Rating Scale

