### Adverse event reporting and harms

tDCS is considered to be a safe technique, but some small risks are recognized. A checklist of potential adverse effects associated with t-DCS administration will be generated with reference to the available literature [28, 29]. All potential risks will be fully disclosed to the participants, along with instructions on how to handle any side effects they may experience. Furthermore, participants will receive a debriefing at the conclusion of each session and will be instructed to contact the principal investigator in the event of any adverse effects resulting from their involvement in the study. In the event of a serious adverse reaction during treatment sessions, local staff (clinic, hospital, institutional) will be promptly notified and emergency protocols will be implemented. We do not expect any adverse events, whether serious or otherwise. However, in the event that one does occur, it will be documented and reported to the local ethics committee of Zhenjiang Mental Health Center.

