## Discussion

In the DSM-5, an ADS has been included for the diagnosis of MDD [30], which is common among MDD patients without comorbid anxiety disorders and correlated with some of their sociodemographic and clinical characteristics [4]. It captures the core symptoms of anxious emotions and cognitions, providing a valuable framework for treatment planning and symptom assessment [4]. The ADS predicts poorer treatment outcomes as shown by higher depression severity, lower remission rates, and greater frequency of antidepressant side effects in patients with MDD on adequate antidepressant treatment; in contrast, the presence of comorbid anxiety disorders did not predict these treatment outcomes [4]. The assessment of anxiety distress according to DSM-5 was found to be significant not only during the acute phase but also in the continuation/maintenance phase of MDD [31]. This simple 5-item specifier holds great potential for clinical utility in the planning and monitoring of treatment for depressed patients; therefore, new and effective interventions beyond pharmacotherapy and psychotherapy are imperative for this subpopulation with heightened illness-associated burden and risks [6].

This randomized controlled trial aims to evaluate the effectiveness of HD-tDCS as augmentation therapy with antidepressants in ameliorating depressive symptoms in MDD patients with ADS. To this aim, the trial compares the effect of HD-tDCS and sham-control HD-tDCS on improving depressive symptoms in addition to the pre-existing antidepressant regimen. The operationalization of depressive symptoms encompasses three levels, specifically the change in depressive symptoms, clinical response, and remission rate as assessed by HDRS-17. The secondary objectives of this study are to evaluate the impact of the intervention on anxiety symptoms, cognitive function, disability resulting from mental disorders, and adverse effects upon completion of the intervention. We also plan to detect any sustained effect by checking the changes at the 2nd week and 6th week after the finished intervention.

The findings of this trial will prove valuable in the management of MDD patients with ADS, as a new safe treatment option is required to alleviate depressive symptoms for those exhibiting inadequate responses to conventional antidepressants. HD-tDCS is anticipated to be efficacious in ameliorating cognitive function and daily functioning, which are frequently compromised in individuals with MDD.

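### The adverse-effect checklist is scheduled only during stimulation, with no use before session 1 or at the 2- and 6-week visits, so new symptoms cannot be reliably separated from old ones and later somatic effects depend on spontaneous report

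*Protocol article*

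**What the plan says.** The abstract and the Discussion list adverse effects among the secondary outcomes. On the instrument, the section on adverse effects and risk indicators says "A checklist of potential adverse effects associated with the administration of HD-tDCS will be compiled based on available literature", and that this checklist "will be utilized to monitor the tolerability and adverse events in each session throughout the intervention". The checklist itself is Additional file 2, which is not shown.

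Table 1, which the protocol presents as the visit schedule for all assessments, has a row "Adverse checklist" with a single mark, under T1. There is none at Screening, T0, T2 or T3. The YMRS row in the same table is marked at Screening, T1, T2 and T3. HDRS-17, DADSI, RBANS and WHODAS 2.0 are each marked from T0 to T3.

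Two other routes collect tolerability data. In the rest period after each session participants "will be actively queried regarding any discomfort they may experience" (Interventions). Under Adverse event reporting and harms, participants "will be instructed to contact the principal investigator in the event of any adverse effects resulting from their involvement in the study", and any event that occurs is documented and reported to the ethics committee.

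Two statements bear on background symptoms. The Discussion says that the anxious distress specifier predicts "greater frequency of antidepressant side effects in patients with MDD on adequate antidepressant treatment". The pilot section reports: "The rate of adverse events(e.g., itching, tingling and headache) showed no significant differences between the two groups".

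**The concern.** A treatment-emergent effect is one that is new, or worse, after treatment starts. To identify it, the same question must have been asked before treatment. Here every participant is on maintenance antidepressants for at least 2 weeks before stimulation, and the protocol itself links this population to more antidepressant side effects. Headache, one of the pilot's named events, can plausibly be present at entry. The checklist is first used once stimulation has begun, so whether a headache is new must be settled by judgement or recall, or not at all.

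The second gap is at the other end. The trial follows participants for 6 weeks after the last session and plans to look for sustained benefit there, but the checklist stops with the sessions. A somatic effect that persists or appears later reaches the data only if the participant both notices it and links it to the study.

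At stake is how the harms comparison can be read. A finding of no difference from sham could mean that the arms are alike, or that background complaints have diluted a real difference. An analysis plan cannot repair this afterwards, because a baseline that was never collected cannot be recovered.

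**Working it through.** **1. The schedule.** The protocol states no figure on this point that could be reproduced, so the first check sets the Table 1 rows side by side. The column labels are not spelled out in the table. From the time points named in Statistical analysis I read T0 as baseline, T1 as end of intervention, and T2 and T3 as 2 and 6 weeks later.

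| Measure | Before stimulation | T1 | T2 | T3 |
|---|---|---|---|---|
| Adverse-effect checklist | none | X | none | none |
| YMRS | Screening | X | X | X |
| HDRS-17 | Screening and T0 | X | X | X |
| DADSI, RBANS, WHODAS 2.0 | T0 | X | X | X |

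The text (each session) and the table (T1 only) agree that use is confined to the intervention. That is 2 of the 2 + 6 = 8 weeks from first session to last visit. The checklist is the only one of these instruments with neither a pre-stimulation value nor a follow-up value.

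**2. What counting pre-existing symptoms would do.** Let *b* be the proportion who already have the symptom, equal in both arms in expectation because of randomization. Let *t* be the true stimulation-phase rate among the rest. If pre-existing symptoms are counted, the observed rate in an arm is

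observed = *b* + (1 − *b*)·*t*

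and the difference between arms is

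(1 − *b*)·(*t*_active − *t*_sham).

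So both absolute rates go up, while the difference shrinks by the factor (1 − *b*).

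**3. Illustration.** Taken from the protocol: 29 per arm (Sample size calculation), and the Fisher exact test, two-tailed at 0.05 (Statistical analysis). Assumed, because the documents do not give them: all event rates and all background rates. Power is exact, summed over all possible tables.

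*True rates 40% active, 10% sham*

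| Background *b* | Active observed | Sham observed | Difference | Power |
|---|---|---|---|---|
| 0 | 40% | 10% | 30 points | 0.68 |
| 0.10 | 46% | 19% | 27 points | 0.49 |
| 0.30 | 58% | 37% | 21 points | 0.26 |
| 0.50 | 70% | 55% | 15 points | 0.14 |

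Worked line for *b* = 0.30: active 0.30 + 0.70 × 0.40 = 0.58; sham 0.30 + 0.70 × 0.10 = 0.37; difference 0.70 × 0.30 = 0.21.

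*True rates 50% active, 20% sham.* The differences are the same (30, 27, 21 and 15 points), and power is 0.57, 0.44, 0.26 and 0.15.

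The factor (1 − *b*) is general wherever existing symptoms are counted. The powers belong to these assumed rates only.

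**4. Follow-up.** Mood and suicidality (HDRS-17), mania (YMRS), anxiety (DADSI), cognition (RBANS) and daily functioning (WHODAS 2.0) are actively rated at T2 and T3. What these leave uncovered is somatic tolerability, such as headache. For that, the only stated route after the last session is the participant's own report of effects seen as arising from the study.

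**The case against.** The case on the other side is substantial, and much of it stands.

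- **A reader might infer that the design favours a claim of minimal side effects. It does not, as far as the missing baseline goes.** The tables above show that counting existing symptoms raises the active-arm rate (40% to 58% at *b* = 0.30), which works against such a claim. The bias is only towards no difference from sham. The abstract and the Discussion speak of minimal side or adverse effects, not of equality with sham. The one statement of no significant difference reports the pilot. The documents do not support attributing a wished-for result to the investigators.
- **A reader might infer that existing symptoms will be counted as events. The documents do not say so.** They give no counting rule, and the unseen checklist may contain an attribution or severity item. A rule for treatment-emergent events may also stand in an analysis plan that is not shown. This is right, but such a rule would still have no scheduled baseline checklist to work from.
- **Follow-up is not empty.** Beyond the YMRS, the scales listed in step 4 are rated at T2 and T3, and risk indicators such as suicidal ideation are to be assessed directly, though without stated timing. Nor is there a causality filter on what is documented once an event is known. The filter lies only in what participants are asked to volunteer.
- **Per-session use suits the main expected effects.** Itching and tingling are plausibly bound to the session, so the baseline problem chiefly concerns headache and similar complaints. The Discussion's remark on antidepressant side effects gives no rate and does not mention headache.
- **The trial is sized on depression severity.** Power for a harms comparison is not a planned property, which is why the figures above serve only to show direction and scale.

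What remains is the schedule itself. It is stated in the protocol, not left open.

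**Conclusion.** The point holds as a design weakness, not as an error or contradiction. The checklist, the only structured tolerability instrument for a secondary outcome, has no administration before the first session and none at T2 or T3, although the visits exist and the YMRS is given a pre-stimulation value and both follow-ups.

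Two consequences follow. Symptoms that can pre-exist cannot be reliably separated from new or worsened ones; if they are counted, the active-sham difference shrinks by (1 − background rate) while both absolute rates rise. And somatic effects after the last session, outside the scheduled scales, depend on spontaneous report, which can only lower the number the checklist captures.

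Under the assumed rates, a background of 10% to 50% reduces a 30-point difference to between 27 and 15 points. The size in this trial is unknown, because the documents give no background rate and no counting rule. The change is worth making because it is cheap and because the baseline cannot be obtained later for anyone already stimulated.

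**What to change.** Give the same checklist, with the same wording, at T0 before session 1, and again at T2 and T3, by the blinded evaluator at the visits already scheduled. Define the analysed outcome as any item new or worse than at T0. At T2 and T3 record all events regardless of presumed cause. Make the Table 1 row agree with the text: T0, each session, T2 and T3.

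The cost is three further uses of an existing checklist, a few minutes each, plus one sentence of definition. The downside is that asking will probably record more events. If recruitment is under way, participants who have already started will lack a T0 value and should be reported as such.
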